### Study aim

The primary aim of this study is to determine the effectiveness of hospital ward care by MDs compared to a patient medical care team consisting of both PAs and MDs. It is hypothesized that due to reallocation of care to a fixed number of PAs per hospital ward, inpatient care becomes more standardized and continued resulting in improved care, which will be reflected by shorter hospital stay. To measure effectiveness we therefore choose length of hospital stay (LoHS) as primary outcome measure. Besides the effectiveness, also the effects on quality and continuity of care and patient and care provider experiences are investigated.

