### Primary outcome

LoHS is the primary outcome measure. Reducing LoHs is important for payers of healthcare and for many patients. LoHS is defined as the time period in days between date of discharge and date of admission. To control for discharge delay for nonmedical reasons, i.e. delay attributable to waiting times for a place in a nursing home or a rehabilitation clinic, or help in the patient’s own home, we also register the date of completion of medical treatment in the hospital.

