### Secondary outcomes

#### Quality of hospital ward care

To assess the quality of ward care, a set of eleven global clinical and process indicators has been selected from the literature and suggestions by a physician panel. The clinical indicators were derived from a national set of indicators for quality of hospital care from the Dutch Health Care Inspectorate (IGZ) [22]. All indicators cover a period of maximum one month after discharge. The selected indicators are:

Clinical indicators:

• Inhospital mortality

• Unplanned transfer to intensive care unit

• Cardiopulmonary resuscitation

• Pressure sore developed during admission

• Fever: number of days body temperature ≥38

• Pain score: number of days Numeric Rating Score ≥7

• Hospital infections: infusion-, urinary track-, airway-, and postoperative wound infections

• Presentation at department of emergency, within one month after discharge

• Non-elective readmission within one month after discharge

Process indicators:

• Days between discharge and letter of discharge

• Introduction hospitalist to the patient less than 24 hours after hospital admission

Data about unplanned readmission and presentation at emergency department after discharge are collected using self-administered patient questionnaires, which are send at one month after discharge date. Information about the other indicators will be retrospectively derived from patient medical records.

#### **
*Patients health-related quality of life*
**

Generic health-related quality of life is measured with the Euroqol-5D (EQ-5D), which is a widely used validated questionnaire containing five domains: mobility, self-care, usual activities, pain, and anxiety/depression [23]. Each domain has three possible levels indicating; no problems, moderate problems or sever problems. Besides, respondents are asked to value their overall health status on a visual analog scale, ranging from 0 (defined as the worst imaginable health state) to 100 (defined as the best imaginable health state). The EQ-5D is assessed by patient questionnaires at three time points: at admission, discharge and one month after discharge.

#### **
*Patient experiences with medical ward care*
**

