### Sample size calculation

To detect a relative difference in LoHS of 20% between the mixed ‘PA/MD model’ and solely ‘MD model’, assuming an average LoHS of 7 days [30], alpha 5%, power 80% and an ICC of 0.06 for patients in same ward, 40 wards including 100 patients each are required. Taking into account an expected drop-out rate of 10% at the level of wards, and a 10% drop out rate of patients (withdrawal of informed consent), 44 wards (22 in each arm) with each 115 patients are included. The number of in depth interviews depends on the moment data saturation is attained.

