### Data analyses

To compare hospital wards utilizing a mixed ‘PA/MD model’ with wards utilizing a solely ‘MD model’, we use logistic regression analyses for dichotomous outcomes and linear regression analysis for continuous outcomes, both with random coefficients to account for statistical clustering of data in hospital wards. The analysis is on an intention to treat basis and matching will be taken into account. Missing values are substituted by multiple imputation techniques. Multivariable models are constructed to correct for potential confounders. Covariables are included in the final model only if they modify the regression coefficient of ward care model (i.e. the central determinant) by more than 10% (regardless of statistical significance of effects). Explorative subgroup analyses per medical specialism will be conducted for each set of at least six wards with similar specialism are included. All estimates are calculated with 95% confidence intervals.

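### Harm after discharge is under-detected: death counts only in hospital, and readmission and emergency visits rest on a one-month questionnaire alone

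*Protocol article*

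**What the plan says.** All references are to the protocol article.

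- **Direction expected.** Study aim hypothesises more standardised and continuous inpatient care "resulting in improved care, which will be reflected by shorter hospital stay". Under Primary outcome, "LoHS is defined as the time period in days between date of discharge and date of admission". The Sample size calculation is built "To detect a relative difference in LoHS of 20% between the mixed" PA/MD model and the MD model, from an average of 7 days.
- **Death.** Quality of hospital ward care lists "Inhospital mortality" and no other death indicator.
- **Readmission and emergency presentation.** The same section says: "Data about unplanned readmission and presentation at emergency department after discharge are collected using self-administered patient questionnaires". The forms go out one month after discharge. The footnote to Table 1 (Economic evaluation) gives the same source. The remaining indicators come from medical records, retrospectively.
- **In-hospital indicators.** One entry begins "Fever: number of days body temperature". Pain is also a count of days, and pressure sores are those arising during the admission. The section adds that every indicator covers at most one month after discharge.
- **Missing data.** Study population has relatives complete forms for patients who cannot, with cognitive impairment as the example. Data analyses says: "Missing values are substituted by multiple imputation techniques".

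**The concern.** If stay falls, a reader will ask whether patients left hospital sooner at no cost or left too soon. The events that separate these readings are death, unplanned readmission and emergency attendance in the following weeks. The plan leaves death outside hospital uncounted. It takes the other two from a form whose return is likely to depend on whether the event happened. Charts are already opened for the other indicators, so the weaker source is used for the outcomes most sensitive to early discharge.

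The planned safeguards do not close the gap. The proxy rule is open-ended about inability to respond but does not address patients who have died. Standard multiple imputation assumes that observed data explain why a value is missing. That is doubtful when death or rehospitalisation is itself the reason, and no exception for death is stated.

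The economic evaluation shares the exposure. Its QALYs use EQ-5D, and its post-discharge costs include readmission and emergency visits, both from the one-month questionnaire. It moves to cost minimisation if effects are judged equivalent.

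Separately, some indicators accrue only while the patient is in hospital, so the primary outcome sets their time at risk.

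**Working it through.** **Inputs from the plan.** Average stay is 7 days and the relative difference is 20%: 0.20 × 7 = 1.4 days, so the target is 5.6 days. Planned enrolment is 44 × 115 = 5,060 patients. The plan gives no figure for any harm indicator, so there is none to reproduce. Its ward number needs an SD that is not stated; it is consistent with about 6.0 days. Nothing below depends on that.

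**1. Which post-discharge events can be seen**

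| Event | Source in the plan | If the patient died or was rehospitalised |
|---|---|---|
| Death outside hospital | none | not counted |
| Unplanned readmission | questionnaire | form less likely to be returned |
| Emergency presentation | questionnaire | form less likely to be returned |
| EQ-5D, GP contacts, home care at one month | questionnaire | same route, same gap |

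**2. Effect of selective non-return (assumed rates).** Let p be the true readmission risk and k the return rate of readmitted patients relative to others. Among returned forms,

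observed risk = p·k / (p·k + 1 − p).

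Take true risks of 10% and 13%, with the same k in both arms:

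| k | observed at 10% | observed at 13% | difference (points) |
|---|---|---|---|
| 1.0 | 10.0% | 13.0% | 3.0 |
| 0.8 | 0.080/0.980 = 8.2% | 0.104/0.974 = 10.7% | 2.5 |
| 0.6 | 0.060/0.960 = 6.3% | 0.078/0.948 = 8.2% | 2.0 |
| 0.4 | 0.040/0.940 = 4.3% | 0.052/0.922 = 5.6% | 1.4 |

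The limit of this illustration matters because the plan uses logistic regression. Observed odds are k × p/(1 − p), so an equal k cancels in the odds ratio, which stays at (0.13 × 0.90)/(0.87 × 0.10) = 1.34. What is lost is absolute risk, absolute difference and number of events. The odds ratio is biased when k differs between arms, and is then multiplied by the ratio of the two k values. With k = 0.6 in the 13% arm and 0.8 in the 10% arm, it becomes 1.34 × 0.6/0.8 = 1.01 (8.2% in both arms), and the true excess disappears. Such a gap could arise if readmissions after earlier discharge were more severe. The document gives no evidence either way.

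**3. Exposure effect on in-hospital indicators.** With a constant daily hazard h, the risk over a stay of L days is 1 − (1 − h)^L.

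| h per day | 7 days | 5.6 days | ratio |
|---|---|---|---|
| 0.5% | 3.4% | 2.8% | 0.80 |
| 1% | 6.8% | 5.5% | 0.81 |
| 2% | 13.2% | 10.7% | 0.81 |

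Raw counts of fever or pain days would scale as 5.6/7 = 0.80. If events instead cluster early, counts per patient are the same in both arms and there is no artefact per patient. Dividing by patient-days would then give 7/5.6 = 1.25 against the shorter-stay arm. Neither scale is safe alone.

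**The case against.** The strongest reply is that the plan does look beyond discharge. Readmission and emergency presentation to one month are named outcomes. EQ-5D, GP contacts, home care and productivity loss are also measured then. Relatives may answer, and missing values are imputed. A questionnaire also captures events at any hospital, which index-hospital charts do not. These indicators are secondary, and details of imputation may sit in an analysis plan that is not shown.

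Much of this stands, and it rules out several stronger readings:

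- A reader might infer that post-discharge harm is largely invisible, or that the study cannot address safety. The named one-month outcomes contradict that; under-detected is the right word.
- A reader might infer that all clinical indicators stop at discharge. Only in-hospital death and pressure sores carry such a limit in their wording. Infections, fever and pain carry none, and the section's one-month statement may extend them.
- A reader might take the 20% fall as established. It needs a constant daily hazard, which the document does not support, and it shrinks if risk is concentrated early.
- A reader might conclude that the dead will be imputed. The text states no exception, but it does not say so either.

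What does not fall is the source of the data, which the article itself fixes. Death after discharge outside hospital is in no indicator, and readmission and emergency presentation have no record-based source.

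**Conclusion.** The point holds as a weakness in secondary outcomes and does not affect the validity of the primary analysis. In a study that expects shorter stay, harm after discharge is under-detected, because post-discharge death is not a listed outcome and the two main signals of early discharge depend on a form that affected patients are least likely to return.

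The size cannot be fixed from the document. On assumed risks of 10% and 13%, a true 3.0-point difference appears as 1.4 to 2.5 points for relative return rates of 0.4 to 0.8. The odds ratio is distorted only if selective return differs between arms. Post-discharge deaths add to the gap by an unknown amount.

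The secondary point also holds. Raw fever and pain days, and in-hospital death and pressure sores, can fall by up to about 20% at the targeted effect without better care, and by less if risk comes early.

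**What to change.** **Main change.** In the planned record extraction, done no earlier than one month after discharge, also record non-elective readmission and emergency presentation at the index hospital, and any recorded death, up to one month after discharge for all consented patients. Combine these with the questionnaire, which still covers events elsewhere. Add two indicators: death from any cause to one month, and death or unplanned readmission to one month. State that values after death are not imputed.

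**Secondary change.** Reconcile the items tied to the admission with the one-month window in Quality of hospital ward care, stating the window for each indicator. Show fever days, pain days, pressure sores and in-hospital death both per patient and per patient-day.

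**Cost.** A few more items on up to 5,060 charts and a later extraction date. Index-hospital records will still miss some deaths and contacts elsewhere, so the gap is reduced and not closed. Reporting response rates by arm would show how much remains.

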In this study we focus on patients admitted to a hospital, who are taken care by a hospitalist. Hospitalists are responsible for the coordination of the daily medical care of hospitalized patients [19]. This role has traditionally been fulfilled by medical residents (MRs) and occasionally by medical specialists. In recent years, the role of hospitalist has been increasingly reallocated to PAs [3,11], facilitated by technological innovations and the standardization of many medical procedures by clinical protocols [20,21]. In 2013, approximately 200 graduated PAs were employed as hospitalist in the Netherlands. When PAs are employed as hospitalists, the applied model to cover 24/7 ward care is often a mixed model that contains both PAs and MDs as hospitalist, comprising a patient medical care team. The tasks of PAs in such a team are comparable to those of the MDs. The PAs, however, tend to work during daytime on weekdays, while MDs often work during evenings, nights and weekends. It is anticipated that within the next decades PAs will be increasingly employed in the management of hospitalized patients for a range of different specialism. However, empirical evidence about the consequences of reallocating medical ward care from MDs to PAs for the quality and safety of care is currently limited.

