### Study setting

Hospital wards are being assigned to the intervention group if the PA has completed an accreditated master’s PA degree and covers at least 51% of the available ward care hours per week during dayshifts (8 h-18 h) on weekdays. Wards are assigned to the control group if solely MDs fulfill the hospitalist position. Exclusion criteria at ward level are: 1) Nurse practitioners (including in training) in the role of hospitalist; 2) Only non-graduated PAs in the role of hospitalist; 3) Psychiatric and pediatric wards and intensive care units. In order to enhance the generalizability of findings we include a heterogeneous sample of hospitals across the country and a mix of medical specialism.

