### Study population

The focus of this study is on the patients admitted to the included hospital wards. Exclusion criteria at patient level are: 1) Patients younger than 18 years; 2) Terminally ill patients; 3) Patients in daycare. Daycare is defined as hospital admissions which are intended to last 24 hours or less. For patients who are not able to fill in questionnaires (e.g. patients with cognitive impairment), family relatives are asked to fill in the questionnaires. Besides the patients, also the PAs, MDs, and a sample of ten nurses who are employed at the included ward are involved as study objects. The sample of nurses is established by selecting the first ten nurses who are scheduled for a dayshift during the third week from data collection.

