Patient experiences with medical ward care are assessed by a self-administered questionnaire at discharge. This questionnaire focuses on satisfaction with communication, experienced continuity of care and cooperation, and the patients view on the medical competencies of the hospitalist. Patient perceptions on communication skills of the hospitalist are measured with the Communication Assessment Tool (CAT), which consists of 15 questions and can be rated on a 5 point Likert scale, ranging from ‘poor’ to excellent’. Although not validated in the Netherlands, the CAT has already proven to be a reliable and valid instrument in the hospital setting in the US [24]. Three subscales from the ‘Chronically Ill Patients Evaluate general Practice’ (CEP) questionnaire were added to measure the items satisfaction with continuity of care, cooperation of ward care providers, and medical competencies of the hospitalist [25]. Each item will be rated on a six point Likert scale, ranging from ‘poor’ to ‘excellent’. As this questionnaire has only been validated for primary care, psychometric properties will be examined in this study. To ensure that patients know who their hospitalist is, we include photos from the hospitalist(s) in the questionnaire. To assess whether patients understood the questions asked in the self-administered questionnaires, we pre-tested the questionnaire in a sample of ten patients admitted to two hospital wards in different hospitals.

#### **
*Health professionals’ work experiences and job characteristics*
**

An online questionnaire is compiled to measure job satisfaction, distress outcomes and other job characteristics of the care providers working at the included hospital wards; i.e. all MDs and PAs who fulfill the role of hospitalist, and a random sample of ten nurses in each of the participating wards.

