*Job satisfaction* is assessed with the McCranie Job Satisfaction Scale, which consists of 13 questions which can be rated on a 6-point Likert scale, ranging from very dissatisfied to very satisfied [26]. The questionnaire addresses satisfaction with the amount of time which is available per patient, satisfaction with the level of work challenge, and satisfaction with the collaboration with nurses, medical specialists and medical residents. Some items were rephrased to make them appropriate for the specific profession of our interest and some questions were added. For all professions we additionally ask about satisfaction with collaboration with PAs. Besides, in the questionnaire for medical specialists a question about satisfaction with time spend on supervision was added, and in the questionnaire for hospitalists we additionally ask for satisfaction with the received supervision. Finally, respondents are asked to value their overall job satisfaction on a visual analog scale, ranging from 1 (extremely unsatisfied) to 10 (extremely satisfied).

*Job stress* is assessed by the 12-item General Health Questionnaire (GHQ-12). The GHQ-12 is a unidimensional, validated scale which comprises questions regarding anxiety, depression, social dysfunction, and loss of confidence. Statements are rated on a 4-point rating scale (symptom present: “not at all” = 0, “same as usual” = 0, “more than usual” = 1, and “much more than usual” = 1) GHQ-12 scores range from 0 to 12 with a higher score indicative of poorer psychological well-being [27].

*Workload* of hospitalists is measured in terms of number of patients seen per day and weekly overtime hours. We ask hospitalists (both PAs and medical residents) and medical specialists for the number of hours per week spend on both direct and indirect patient contacts at the hospital ward, and the number of hours per month spend on non-patient related tasks like participating in quality and patient safety projects and performing scientific research. In the questionnaire for hospitalists we additionally ask for the number of hours spend on patient related non-hospitalist tasks like performing medical procedures or supporting outpatient care. Besides, we ask the hospitalists how much supervision time they obtain, and the medical specialists how many time they spend on supervision.

#### **
*Continuity of care*
**

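### The nurse sample is called random, but the stated rule takes the first ten on the week-3 dayshift roster, which favours nurses with many dayshifts and possibly those with more PA contact

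*Protocol article*

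**What the plan says.** Two sections of the protocol article describe the nurse respondents.

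- **Study population** states that "a sample of ten nurses who are employed at the included ward are involved as study objects" and gives the selection rule: "selecting the first ten nurses who are scheduled for a dayshift during the third week from data collection".
- **Secondary outcomes, Health professionals' work experiences and job characteristics** lists who receives the online questionnaire: all MDs and PAs acting as hospitalist, and "a random sample of ten nurses in each of the participating wards".

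Three further statements bear on what the rule selects.

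- **Background** says of PAs and MDs: "The PAs, however, tend to work during daytime on weekdays, while MDs often work during evenings, nights and weekends".
- **Study setting** makes a ward an intervention ward if the graduated PA "covers at least 51% of the available ward care hours per week during dayshifts (8 h-18 h) on weekdays".
- The job satisfaction text under Secondary outcomes adds an item: "For all professions we additionally ask about satisfaction with collaboration with PAs".

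**The concern.** A fixed roster-order rule and a random sample are different designs, and the article claims the second while specifying the first. A report that repeats the word random would give the nurse sample a property it does not have.

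The difference is more than a label. The rule ties a nurse's chance of selection to the number of dayshifts worked in one week. Daytime is also when PAs are mainly present, so the variable that drives selection is linked to the intervention. Nurse job satisfaction, distress and, above all, satisfaction with collaboration with PAs could therefore lean towards nurses who meet the PA often. The mixed model is described in Background as a way to cover ward care around the clock, so nurses who work mostly outside PA hours also belong to the team under evaluation.

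**Working it through.** **1. The two descriptions side by side.** Under a random draw of ten from N nurses, each nurse has inclusion probability 10/N. Under the Study population rule, a nurse with no dayshift in the third week has probability 0, and the others depend on how early in that week their first dayshift falls. The two agree only if selection chances happen to be about equal across nurses, which nothing in the article ensures.

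**2. How unequal could selection be? (Illustration; all roster inputs are assumed.)** The article gives no ward team size, rotation pattern or share of nurses without a dayshift. Assume that 20% of nurses have no dayshift in week 3 and that the rest have 1 to 5 with equal probability, on random days of the seven. Nurses are taken in order of first dayshift, with ties within a day broken at random. Simulated inclusion probabilities:

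| Nurses on ward | No dayshift | 1 dayshift | 3 dayshifts | 5 dayshifts | Random draw, 10/N |
|---|---|---|---|---|---|
| 20 | 0 | 0.28 | 0.67 | 0.88 | 0.50 |
| 30 | 0 | 0.15 | 0.41 | 0.67 | 0.33 |
| 40 | 0 | 0.10 | 0.31 | 0.52 | 0.25 |

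Under these assumptions, in a ward of 30, a nurse with five dayshifts is about 0.67/0.15 = 4.5 times as likely to be chosen as a nurse with one.

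**3. What could this do to a ward mean?** Let f be the share of nurses with no dayshift that week and d the difference in mean score between nurses with and without a dayshift, in SD units. Leaving out the share f shifts the ward mean by f × d. For assumed f of 0 to 0.40 and d of 0 to 0.5:

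- f = 0 or d = 0: shift 0
- f = 0.20, d = 0.5: 0.20 × 0.5 = 0.10 SD
- f = 0.40, d = 0.5: 0.40 × 0.5 = 0.20 SD

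This counts only exclusion, not the unequal weighting among nurses who do have dayshifts.

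**4. What could it do to the comparison of arms?** With the same f in both arms, the bias is f × (d in PA/MD wards − d in MD wards). It is zero if every nurse has a dayshift that week, or if the dayshift difference is equal in both arms. Over the assumed ranges it lies between −0.20 and +0.20 SD, so even its sign is open.

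**5. Scale.** Ten nurses in each of 40 wards is 400, and in each of the 44 wards of the Sample size calculation is 440. This is the whole invited nurse sample, not a count of nurses wrongly included or left out.

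**The case against.** The strongest reply is that this is a wording slip with little consequence. Much of that reply stands.

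- The article does not say whether nurses rotate. If most do, nearly all have a dayshift in week 3 and the sample may be close to representative.
- Only nurses with no dayshift in that week are certain to be left out. A nurse who works mainly evenings, nights or weekends is still eligible with a single dayshift, and the rule does not restrict dayshifts to weekdays.
- The rostered shift only identifies the nurse. The questionnaire asks about the job in general and is not tied to that shift.
- The rule is the same in both arms, and data collection runs in parallel within matched pairs.
- Sampling dayshift nurses is defensible in itself, since the intervention is defined by cover of weekday dayshifts.

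Two stronger readings are tempting. A reader might infer that the nurse results do not represent the ward team; that needs roster facts which the article does not contain. A reader might also set the minimum PA cover as a share of the week (0.51 × 50 h = 25.5 h; 25.5/168 = 15%) against a nurse sample drawn wholly from dayshifts. That compares hours with people, treats a minimum as the actual cover, and measures no bias.

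The reply does not remove the contradiction itself or the unequal chance of selection. A common rule cancels in the comparison only under the conditions in step 4, and an intervention concentrated in the daytime gives some reason to doubt that the dayshift difference is equal in both arms.

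**Conclusion.** The contradiction is certain: the article states a property, randomness, that its own selection rule lacks. It is also certain that nurses without a week-3 dayshift cannot be selected. That nurses with many dayshifts are favoured follows whenever dayshift frequency varies between nurses. That nurses with PA contact are over-represented is plausible from Background and Study setting, but it is a risk and not a demonstrated fact.

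The size and direction of any between-arm bias cannot be derived; the figures above rest on assumed rosters. The reach is limited to secondary nurse-reported outcomes, most directly satisfaction with collaboration with PAs. The primary outcome is unaffected. The point is worth correcting because the remedy is specific and cheap, not because a large bias has been shown.

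**What to change.** Draw the ten nurses at random, by computer, from the list of all nurses employed on the ward, whatever their shifts, by the same procedure in both arms. Put this one description in Study population and in the subsection on health professionals' work experiences. The sample size and the online questionnaire stay as they are. The cost is obtaining the full nurse list of each ward instead of only the week-3 dayshift roster. Recording each nurse's usual shift pattern would let readers see whom the sample covers.

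If the nurses have already been selected, drop the word random, describe them as a consecutive sample of dayshift nurses, and limit the conclusions on nurse outcomes accordingly. That costs only the change of text.
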